## LIST OF ABBREVIATIONS

|               |                                                                                                                                         |
|---------------|-----------------------------------------------------------------------------------------------------------------------------------------|
| ACCORD | Academic and Clinical Central Office for Research & Development - Joint office for The University of Edinburgh and Lothian Health Board |
| CI     | Chief Investigator                                                                                                                      |
| CRF    | Case Report Form                                                                                                                        |
| GCP    | Good Clinical Practice                                                                                                                  |
| ICH    | International Conference on Harmonisation                                                                                               |
| PI     | Principal Investigator                                                                                                                  |
| QA     | Quality Assurance                                                                                                                       |
| REC    | Research Ethics Committee                                                                                                               |
| SOP    | Standard Operating Procedure                                                                                                            |
| OCT    | Optical Coherence Tomography                                                                                                            |

# 1 INTRODUCTION

## 1.1 BACKGROUND

Circulatory shock is a non-specific pathophysiological state constituting systemic tissue hypoperfusion. Aetiological subgroups of circulatory shock states can be considered. Broadly, these include: (1) hypovolaemic shock: hypoperfusion following haemorrhagic or non-haemorrhagic (e.g., third-space fluid loss) intravascular depletion; (2) cardiogenic shock: secondary to insufficient cardiac output (e.g., mechanical, cardiomyopathic or arrhythmogenic pathologies); (3) obstructive shock: following extra-cardiac pump failure, commonly right-sided following massive pulmonary embolism; and (4) distributive shock: loss of peripheral vascular resistance. Distributive shock can follow diverse pathologies, commonly these include sepsis, severe inflammatory response syndrome (SIRS), neurogenic, anaphylactic, and toxic pathologies. A fifth aetiology of circulatory shock, endocrine, occurs in patients suffering Addisonian or thyrotoxic crises. However, the mechanisms of this have not been fully elucidated and there is substantive pathophysiological overlap with the aforementioned aetiologies.

Holistically, circulatory shock represents a large proportion of morbidity and mortality in acute care settings. In 198 European intensive care units (ICUs, n=3147 patients) Sakr et al. estimated that 1 in 3 patients experienced some type of circulatory shock throughout the course of their ICU admission(1).

Indeed, septic shock and resultant multi-organ failure has been a prominent cause of COVID-19 mortality within ICU settings(2). Although the global burden of circulatory shock in this setting is unlikely to be fully elucidated, in Wuhan approximately 35% of patients of all COVID-19 patients between December 2019 and 26th January 2020 received vasopressor support(3). Furthermore, 95% of patients receiving invasive mechanical ventilation in New York, between the 3rd and 27th of March 2020 received similar vasoconstrictive support(4).

Current management of circulatory shock is targeted at improving vascular perfusion. Other than in obstructive shock, this involves inotropes and vasopressors to support cardiac output and systematic vascular resistance, with fluid resuscitation indicated in distributive, hypovolaemic and certain endocrine settings (e.g., an Addisonian crisis) to further improve cardiac output through increased intravascular volume, venous return and thus preload.

This treatment philosophy assumes that the microvascular environment is reflective of macrovascular conditions. Microcirculatory dysfunction has been well characterised in both in-vitro and in-vivo settings, the MICROSHOCK study found sublingual perfused vessel density (a measure of microcirculatory function) a better discriminator for multiorgan failure in patients with traumatic haemorrhagic shock: area under curve 0.87 (0.76-0.99) compared with highest recorded lactate 0.69 (0.53-0.84) and cardiac index 0.66 (0.49-0.83)(5). Indeed this dissociation between micro- and macro-circulation may explain the therapeutic failure of early goal-directed therapies (EGDTs), which sought to aggressively pursue macrovascular physiological parameters(6). Although an initial study demonstrated significant reduction in in-hospital mortality, this was not replicated in subsequent validation studies or in individual patient meta-analysis(6–10). The additional 48-hour mortality associated with aggressive fluid resuscitation in African paediatric patients with severe febrile illness highlights how overly aggressive fluid resuscitation may have a deleterious impact on patient outcomes(11).

## 1.2 RATIONALE FOR STUDY

Recent advancements in optical coherence tomography (OCT) highlighted its potential as a non-invasive, safe, feasible and valid approach to observe and quantify intraocular structures in supine, critically ill, patients(12). The retinal and choroidal vascular beds represent novel microvascular sample sites. Previous microvascular physiological studies in circulatory shock have focussed on sublingual, buccal,

gastric, muscular, and subcutaneous capillary beds  
however the microvascular circulation is a highly heterogenous environment making interpretation in the clinical setting challenging. (5,13–17).

As part of the physiological response to shock or vasopressor therapy (e.g., norepinephrine) and mediated through the distribution of adrenergic receptors in arterial smooth muscle cells, peripheral and then visceral organ perfusion is sacrificed to preserve central neurological (including ocular structures) and cardiopulmonary function(18). Consequently, we hypothesise that microvascular blood flow in the intra-ocular retinal and choroidal vascular beds will provide a better representation of the vascular environment in vital organs such as the brain, heart and lungs in patients experiencing circulatory shock.

We are trying to develop a hand-held, point of care monitoring device based on optical imaging. As a first step in understanding whether microcirculatory changes in the intra-ocular vasculature can be used to monitor shock progression in critically ill adults, we aim to perform OCT imaging of a heterogenous group of intensive care and high dependency unit patients, to ascertain whether variation in retinal and choroidal structure correlates with disease state and physiological status.

Ultimately, it is hoped that better monitoring of patient fluid status will enable patient-level physiological optimisation of fluid resuscitation, preventing excess morbidity due to fluid overload within the critically ill patient population.

## **2 STUDY OBJECTIVES**

### **2.1 OBJECTIVES**

#### **2.1.1 Primary Objective**

To observe OCT appearances of the retina and whether they differ according to fluid balance (cumulative or 24-hour), blood pressure, and circulatory shock diagnosis, in a heterogenous cohort of critically ill adult patients.

#### **2.1.2 Secondary Objectives**

1. To observe changes in retinal OCT measurements in critically ill adult patients over time (over a 24-hour observation period)
2. To assess the feasibility of and image quality (by blinded assessors) from performing OCT in a critical care environment, using the Heidelberg Spectralis Flex Module.
3. To assess and attempt to model for possible measurement errors in performing these OCT measurements (e.g., variation in X-, Y-, Z-axis alignment of the probe when attempting visualisation).

### **2.2 ENDPOINTS**

#### **2.2.1 Primary Endpoint**

Retinal and choroid thickness measured by OCT

#### **2.2.2 Secondary Endpoints**

Change in retinal and choroid thickness between first (baseline) and second measurement (12-72 hours later).

### **3 STUDY DESIGN**

D-RISC-ii is an observational study that will run for 12 months within the critical care unit (comprising intensive care and high dependency care beds) at a single institution (Royal Infirmary of Edinburgh).

Initially, the study will function with a case-series approach, identifying patients, visualising their retinal and choroidal beds with optical coherence tomography, collecting exposure data, and assessing the feasibility of further works in this setting. The primary outcome incorporates a cross-sectional element, as we will attempt to characterise patients with to pre-specified exposure features (circulatory shock diagnosis, blood pressure, fluid balance), according to the dimensions of retinal and choroidal structures, at the initial recruitment sampling timepoint. Our secondary outcome follows a cohort approach, seeking to identify variation in these choroidal and retinal parameters according to exposure.

### **4 STUDY POPULATION**

#### **4.1 NUMBER OF PARTICIPANTS**

We will seek to recruit patients from intensive care and high dependency treatment units at one site over a one-year period. We do not propose a maximum number of patients over this time period.

##### **INCLUSION CRITERIA**

1. At least 16 years old AND
2. Admitted to intensive care (ICU) or high-dependency care units (HDU) AND
3. A requirement for Intensive Care Society Level 2 or 3 care will be eligible to participate(19).

#### **4.2 EXCLUSION CRITERIA**

Patients may be excluded for any of the following criteria:

1. Patient refusal
2. Next of kin or power of attorney unavailability or refusal
3. Anticipated survival <24 hours
4. Pregnancy
5. Confirmed or suspected conditions where there is a clinical exclusion for pupillary dilation: e.g., traumatic brain injury, meningitis, cerebrovascular accident, space-occupying lesion (tumour, encephalitis etc.).
6. Ophthalmologic conditions: facial trauma precluding visualization of both retinas.
7. Imaging not feasible (equipment/ researcher unavailable or disruptive to care provision).

### **4.3 CO-ENROLMENT**

As this study is non-interventional, with limited additional burden to participants (beyond standard care of care in intensive care/ high dependency units), participant co-enrolment will be permitted with other non-interventional and interventional studies. However, to mitigate against unforeseen circumstances, co-enrolment will require mutual agreement between CIs and the Sponsor as per the ACCORD co-enrolment policy.

## **5 PARTICIPANT SELECTION AND ENROLMENT**

### **5.1 IDENTIFYING PARTICIPANTS**

Patients requiring treatment in intensive care (ICU) or high dependency (HDU) units will be identified and screened for eligibility by members of the clinical care team (medical student, nurses, research nurses and physicians).

Once eligibility has been confirmed, the patient or their legal representative (under Adults with Incapacity (Scotland) 2000 Act) will be approached and information about the study provide in written and verbal form. The initial approach will be made by a member of the clinical care team (embedded medical student, research nurses and physicians) with the agreement of the treating physician.

### **5.2 CONSENTING PARTICIPANTS**

#### **A. Individuals with capacity:**

Members of the research team will periodically be available to answer any queries and clarify understanding. Subsequently, if agreeable, formal written consent will be requested and documented on the patient's notes.

#### **B. Individuals without capacity:**

Where potential participants are considered not to have capacity to consent, consent will be sought from their legal representative under the Adults with Incapacity (Scotland) 2000 Act. Members of the research team will periodically be available to answer any queries and clarify understanding. Subsequently, if agreeable, formal written consent will be requested and documented on the patient's notes.

If the representative is not available in-person at any stage, information will be provided and consent sought by telephone by an experienced/ trained member of the clinical care team (research nurse, senior registrar or consultant) and witnessed by another member of the team. Verbal consent will then be documented in the patient's notes and written consent sought at the first convenient opportunity as above. To minimise distress, representatives will only be approached by telephone with the agreement of the treating physician.

#### **C. Participant regains capacity:**

Upon regaining capacity, follow-up consent will be obtained as quickly as feasibly possible, as outlined in Part A.

#### **5.2.1 Withdrawal of Study Participants**

Participants are free to withdraw from the study at any point or a participant can be withdrawn by the Investigator. If withdrawal occurs, the primary reason for withdrawal will be CR007-T02 v4.0

documented in the participant's case report form, if possible. The participant will have the option of withdrawal from:

(i) all aspects of the trial but continued use of data collected up to that point. To safeguard rights, the minimum personally identifiable information possible will be collected.

## 6 STUDY ASSESSMENTS

### 6.1 STUDY ASSESSMENTS

| Assessment                                                                                                | Screening                           | Baseline Visualisation              | Repeat Visualisation (after 12-72 hours) |
|-----------------------------------------------------------------------------------------------------------|-------------------------------------|-------------------------------------|------------------------------------------|
| Assessment of Eligibility Criteria                                                                        |  |                                     |                                          |
| Written informed consent                                                                                  |  |                                     |                                          |
| Contact details                                                                                           |  |                                     |                                          |
| Demographic data (e.g., age, sex, race)                                                                   |  |                                     |                                          |
| Date/time of hospital admission                                                                           |                                     |  |                                          |
| ICU/ HDU admission                                                                                        |                                     |  |                                          |
| Date/time of ICU/HDU admission                                                                            |                                     |  |                                          |
| Diagnosis at admission and any renal, cardiovascular, hepatic, pulmonary or ophthalmologic comorbidities. |                                     |  |                                          |
| Changes in diagnosis/ status                                                                              |                                     |  |       |
| Fluid balance (24-hour and cumulative)                                                                    |                                     |  |       |
| Clinical assessment of fluid balance                                                                      |                                     |  |       |
| OCT                                                                                                       |                                     |  |       |
| OCT measurements (time, date, eye dilated, angle of bed, prone/ supine)                                   |                                     |  |       |
| Adverse events to study protocol                                                                          |                                     |  |       |
| Organ supportive therapies                                                                                |                                     |  |       |
| Most recent BMI                                                                                           |                                     |  |       |
| Most recent APACHE II                                                                                     |                                     |  |       |
| 24-hour mean PaO 2 , Lactate, FiO 2 , CRP.                                          |                                     |  |       |
| Pre-sample SaO 2 , RR, HR, systolic BP,                                                        |                                     |  |       |

|                                                                          |  |                                     |                                     |
|--------------------------------------------------------------------------|--|-------------------------------------|-------------------------------------|
| MAP, Temp, GCS.                                                          |  |                                     |                                     |
| Most recent reticulocytes, haemcrit, Hb, WBC, albumin, serum osmolality. |  |  |  |

## 7 DATA COLLECTION

Data will be collected by members of the research team including named medical students and research nurses and supervised by the CI and qualified by training, experience, and good clinical practice (GCP) certification.

The OCT operator will receive training to operate the unit. Imaging should take no longer than 15 minutes and is non-invasive.

### 7.1 Source Data Documentation

Data will come from the following sources:

1. The electronic patient record (EPR)
2. Paper-based patient records (including clinical observation charts)
3. Direct recording of clinical observations from patient monitors
4. Clinical examination
5. Optical Coherence Tomography (OCT) measurements.

### 7.2 Case Report Forms

Paper-based case report forms will be used to collect data from sources 1-4. These will be stored together in a locked cupboard in a locked research office in the Royal Infirmary of Edinburgh.

Optical coherence tomography visualisations (from source 5) will be retained locally on an encrypted system that accompanies the Heidelberg Spectralis Flex Module.

#### 7.2.1 Personal Data

We will retain patient name, contact details (including address, email address (if possessed) and contact phone number) on the paper-based case-report form. If necessary, we will also retain similar contact details for the participant's representative under Adults with Incapacity (Scotland) 2000 act for the purposes of contacting them during the research. other measures collected during the study will be non-identifiable. Identifiable data will be linked with an anonymised study database through a unique identification number.

The paper-based case-report form (and the corresponding study index identifier) will be stored by the research team within a secure filing cabinet within a locked room within NHS Lothian onsite at the Royal Infirmary of Edinburgh. [name], [name] and [name] (medical student) and other authorised study personell will have access; however, this will be controlled by [name] (Chief Investigator).

## 7.2.2 Data Information Flow

Patient identifiable data will be collected when informed consent is obtained at screening and CHI number will be used to identify the participant during data collection and stored on paper-based case report forms.

Clinical data (Sources 1-4) will be collected on paper-based case report forms (including identifiers). These will be stored at the NHS Lothian onsite (locked facilities where access is restricted to within the research team). This data will be stripped of patient identifying information, indexed by study index identifier, and transcribed into an excel spreadsheet on the NHS Lothian server. Subsequently, this anonymous data will be transferred by secure file transfer protocol to a University of Edinburgh server at the Roslin Institute.

OCT visualisations (Source 5) will initially be stored locally on an encrypted system that accompanies the Heidelberg Spectralis Flex Module. These images will be anonymised and indexed by study index identifier. Following connection of the Heidelberg Spectralis Flex Module to a University of Edinburgh server, the anonymised visualisations will be transferred to the retinal image database which is a located on secure server within the Edinburgh Imaging QMRI facility at the University. Analysis of images will be conducted within the Image Analysis Core laboratory in QMRI using the Heidelberg HeyEx software and the outputs will be transferred to a secure server by password protected data sharing using the University's DataSync system for further analysis at the Roslin Institute under the supervision of [name].

Patient identifiable data will be destroyed after 3 years. All other study data will be destroyed after 10 years.

[figure not shown]

EPR: Electronic Patient Record; OCT: Optical Coherence Tomography; UoE: University of Edinburgh; QMRI: Queen's Medical Research Institute

## 7.2.3 Transfer of Data

Anonymised visualisations and anonymised participant data may be shared with researchers at other institutions, but any data sharing will be subject to the negotiation of a suitable data-sharing agreement.

#### **7.2.4 Data Controller**

The University of Edinburgh and NHS Lothian are joint data controllers along with any other entities involved in delivering the study that may be a data controller in accordance with applicable laws (e.g., the site)

#### **7.2.5 Data Breaches**

Any data breaches will be reported to the University of Edinburgh and NHS Lothian Data Protection Officers who will onward report to the relevant authority according to the appropriate timelines if required.

## **8 STATISTICS AND DATA ANALYSIS**

### **8.1 SAMPLE SIZE CALCULATION**

The initial feasibility study (D-RISC) only recruited 2 patients but demonstrated feasibility with some adjustments to the protocol (which have now been implemented, such as less frequent monitoring and a boom operated OCT device).

Consequently, this sample size (at least 15 patients) is one of convenience to allow adequate characterisation of the intra-ocular vasculature of critically ill patients. Once 15 patients have been recruited, we will undertake an interim analysis to consider whether recruitment of additional patients would increase the validity of the dataset.

### **8.2 PROPOSED ANALYSES**

Summary measures to be reported:

As per section 6.1, 35 summary and exposure parameters will be collated throughout the duration of the study.

Method of analysis:

Manual grading of quality of intra-ocular visualisations with OCT will be performed, with unsatisfactory visualisations removed from the dataset.

Quantification of choroidal and retinal thickness will be performed with automated image processing techniques.

Where only an initial set of measurements is captured from a participant, we will not attempt to impute missing values. Instead, we will only analyse that data with respect to other initial captures.

Univariate and multivariate analysis of intra-ocular measurements against clinical data points to ascertain possible differences with respect to our predefined subgroups: patient fluid balance indices (cumulative and 24-hour), blood pressure, and a clinical diagnosis of circulatory shock at initial measurement (according to intention-to-treat principle).

An interim analysis will be performed after data from 15 patients has been recorded to establish whether a larger sample size is necessary to increase the validity of the dataset.

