## **11.8 CONTINUATION OF TREATMENT FOLLOWING THE END OF STUDY**

This is an observational study and thus there will be no treatment to continue.

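### Section 8.2 fixes shock status at the first scan under an intention-to-treat label, so the change endpoint pools resolved with persisting shock

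*Protocol*

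**What the plan says.** The study is observational: "D-RISC-ii is an observational study that will run for 12 months within the critical care unit" (section 3), and section 11.8 confirms that no treatment is given under it: "This is an observational study and thus there will be no treatment to continue".

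Section 3 sets out two analyses. The primary one is cross-sectional, relating thickness to shock diagnosis, blood pressure and fluid balance "at the initial recruitment sampling timepoint". The other is longitudinal: "Our secondary outcome follows a cohort approach, seeking to identify variation in these choroidal and retinal parameters according to exposure". Section 2.2.2 defines its endpoint as the change in retinal and choroid thickness between the first scan and a second one 12 to 72 hours later.

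Section 8.2 holds the only analysis text. It names "our predefined subgroups: patient fluid balance indices (cumulative and 24-hour), blood pressure" and then "a clinical diagnosis of circulatory shock at initial measurement (according to intention-to-treat principle". It names no analysis that uses shock status at the second scan or a change in any exposure.

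Section 6.1 collects at both scans the changes in diagnosis or status, systolic and mean arterial pressure, and "Fluid balance (24-hour and cumulative" balances. The rationale in section 1.2 calls the study a first step towards knowing whether ocular changes "can be used to monitor shock progression in critically ill adults".

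**The concern.** Intention-to-treat keeps patients in the group to which they were assigned, so that a randomised comparison survives later departures from treatment. With no assignment there is nothing to preserve. At the first scan a patient has only one shock status, so the label changes nothing there. It has an effect only over follow-up, where it holds a patient in the first-scan category whatever happens next. The rule therefore reaches the change endpoint.

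A patient who leaves shock before the second scan and one who stays in shock are then in the same group. That is the distinction a monitoring measure has to make. The planned contrast would blend the strength of the link between thickness and shock with the rate of recovery in this sample, although the data to separate the two are on the case report form.

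**Working it through.** The plan gives no effect size, standard deviation, power or recovery rate, so there is no figure of its own to reproduce. The check is an illustration on stated assumptions.

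**Inputs**
- Two scans, 12 to 72 hours apart: protocol section 2.2.2.
- Shock status fixed at scan 1: section 8.2.
- Assumed: thickness = subject effect + delta x current shock status + measurement error.
- Assumed: a share r of patients in shock at scan 1 are out of shock at scan 2, and a share n of the others develop shock.

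**Change contrast by first-scan shock**
- Mean change, shocked at scan 1: -r x delta.
- Mean change, not shocked at scan 1: +n x delta.
- Difference: -(r + n) x delta. With no new shock (n = 0) this is -r x delta.

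| r | n = 0 | n = 0.10 |
|---|---|---|
| 0.25 | -0.25 delta | -0.35 delta |
| 0.50 | -0.50 delta | -0.60 delta |
| 0.75 | -0.75 delta | -0.85 delta |

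If nobody changes status (r = n = 0), the contrast is zero however strongly thickness depends on shock. Quite different situations can also give the same answer: with n = 0, r = 0.25 and delta = 1 gives -0.25, and so does r = 0.50 with delta = 0.5.

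**Contrast that uses status at both scans**
- Among patients shocked at scan 1, the mean change is -delta if resolved and 0 if persisting. The difference is -delta, whatever r is.
- Regressing change in thickness on change in status estimates delta directly. A simulation of 400,000 subjects, one third shocked at scan 1, with delta = 1, reproduced the table and returned 1.0 delta at all six settings.

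**Precision at the planned minimum**

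Section 8.1 plans at least 15 patients. Assume 80% power, two-sided 5%, a normal approximation and two usable scans in every patient. The detectable difference in SD units is (1.96 + 0.84) x sqrt(1/a + 1/b):
- 5 against 10: 2.80 x 0.548 = 1.53.
- Equal split (7.5 each): 2.80 x 0.516 = 1.45.

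Resolved against persisting uses only patients shocked at scan 1, so it is less precise still.

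**The case against.** The strongest reply is that change by baseline exposure is a legitimate cohort contrast, and section 3 calls the secondary outcome a cohort approach. Section 8.2 also speaks generally of analysing ocular measurements against clinical data, which include changes in status, and prohibits nothing. Model detail for a secondary endpoint often sits in a separate analysis plan. Section 1.2 describes only a first step, whose immediate aim is correlation with disease state. Most of this stands, and it limits the point. It does not rescue the label or the fixed shock definition: both are stated in the protocol and would carry into any later plan.

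Four stronger readings are tempting and not supported.

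- *The change analysis cannot show tracking.* Too strong. First-scan shock may predict later change, and the data for a better analysis are collected.
- *Fluid balance and blood pressure are frozen too.* On the nearest reading, the words about initial measurement qualify only the shock diagnosis. The wider reading is possible, so the text is unclear rather than wrong.
- *The contrast shrinks to 80%, 60% or 40% when 20%, 40% or 60% of shock resolves.* That is the between-group contrast at scan 2, (1 - r) x delta, which the plan does not specify. Under the same model the change contrast is -r x delta, so its size grows as more shock resolves.
- *The 24-hour fluid window does not fit the interval.* At 12 hours the two windows share 24 - 12 = 12 hours; at 72 hours the second covers 24/72, one third of the gap. But the plan lists cumulative balance beside the 24-hour figure and nowhere relies on the latter alone to explain change.

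**Conclusion.** The point holds for shock status and the change endpoint. The intention-to-treat label has no meaning without assignment, and its working effect is to pool resolved with persisting shock. If thickness follows current status and no new shock arises, the planned contrast equals -r x delta and cannot by itself separate recovery rate from strength of tracking. The values of r, n and delta are assumptions; the protocol gives none. The primary cross-sectional analysis is unaffected, because first-scan exposure is the right choice there. For fluid balance and blood pressure the defect is one of clarity only. This should be corrected, but it is a repair to the wording of a secondary analysis and does not threaten the study.

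**What to change.** In section 8.2:

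1. Delete the reference to intention-to-treat.
2. State that first-scan exposure applies to the cross-sectional analysis, and say whether this covers all three exposures.
3. For the change endpoint, keep change by first-scan shock as a cohort contrast, and add change in thickness against change in exposure: cumulative fluid balance at scan 2 minus scan 1 (both counted from the same start), change in mean arterial pressure, and shock status at both scans. For shock, resolved against persisting is enough, or a mixed model with time-updated exposure. A four-way split into persisting, resolved, new and never would be barely estimable with about 15 patients.
4. Report these results descriptively, as estimates with intervals.

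The cost is one paragraph and a few more secondary analyses, which will be imprecise at this sample size. No new data are needed: fluid balance and pressure are recorded at both scans, and second-scan shock status comes from the section 6.1 entry on changes in diagnosis or status.
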